**Fig. 3 Fig3:**
[figure not shown]
Consort flowchart

Due to the nature of the intervention and study design, neither the study subjects nor the research and program staff were blinded. However, the study was designed to minimize measurement bias. Additionally, all research interviewers were trained on the importance of uniform interview procedures. Drs. [name], [name] and [name] were responsible for the training and supervision of these research interview staff.

Qualitative data was collected from a subsample of intervention couples (*n* = 50 couples) and CHARM-trained VHPs (*n* = 16 VHPs) who conducted any sessions, in order to provide further insight into outcome findings. At 18 month follow-ups, 2 randomly selected participating couples from each intervention village (*n* = 50 couples total) were asked to participate in in-depth interviews. The interviews were jointly conducted by the NIRRH team of 1 male and 1 female who also conducted the survey separately with the couple. Only couples who participated in all 3 sessions (including wives in session 3) were eligible for qualitative interview participation, biasing the perspectives on the intervention but allowing for insight into the utility of the full program. The in-depth interview guideline for couples assessed respondents’ perceptions of how their relationship and family planning practices changed since participating in the program and how the intervention created or affected these changes. Interviews were 45–60 min in length and conducted in Marathi. CHARM-trained VHPs who delivered sessions (*n* = 16) also participated in in-depth interviews subsequent to study completion. The 30 min open-ended interviews with intervention VHPs assessed their perceptions of how CHARM affected the couples with whom they met and whether behavior changes and ongoing contact for family planning services continue subsequent to the intervention. They were also asked about the strengths and weaknesses of the program. Data were collected and analyzed using the same methods as described above for formative research.

#### Quantitative measures

Baseline and follow-up surveys were collected from couples using measures based on India’s Demographic and Health Surveys (DHS/India’s NFHS-3) [1] or other validated measures (indicated in Table 2).

**Table 2 Tab2:** Quantitative measures

Variable	Description
Demographics	age, caste, religion, education, literacy, income, employment, and living conditions
Marital Factors	age at and length of marriage, frequency of sexual activity marital communication
Fertility and FP History	age at first pregnancy, number and timing/wantedness of pregnancies and childbirths, sex of children, current breast feeding, FP history (timing and type of contraceptives used).
Fertility/FP normative beliefs and ideologies	ideal number of children, in total and based on sex (parity, son preference); Attitudes toward contraception, contraceptive knowledge, desire for and intent to use traditional and/or modern contraceptives (by type), and perceived access to all forms of contraception
Sexual risk behaviors	past year sexual infidelity or sex work involvement, condom use in these contexts
Male Gender Equity Norms (only men asked)	15 item scale measured male gender norms related to sexual and reproductive health, sexual relations, violence, domestic responsibilities, and homophobia. Gender-Equitable Men Scale [38] (CHARM Cronbach alpha .72);
Male Partner Violence^a^ (only women asked)	11 items assessed physical and sexual marital violence, ever and in past 12 months. (CHARM Cronbach alphas .82–.92 across subscales)
Acceptability of spousal violence	two scales of 8 and 10 items assessed reasons for acceptability of spousal physical and sexual violence. CHARM Cronbach alpha .82 &. 92, respectively
FP behaviors	item assessed contraception used (e.g., withdrawal, condom, IUD, sterilization, etc.) in the past 3 months. Item assessed discussion of contraceptive use with spouse.
Pregnancy and Pregnancy Intent	data on current pregnancy was obtained via a urine test for human chorionic gonadotropin (HCG) at baseline and 18 month follow-up. Survey data also captured self-reported pregnancy and whether they want to become pregnant then, later, or not at all.

^a^Items on spousal violence were only be assessed for women for purposes of her safety in accordance with guidelines for domestic violence research from the World Health Organization [37]

Intervention participants also completed a brief survey at follow-up on their experiences with the intervention, including FP content covered in sessions, delivery of contraceptives, perceptions of the strengths of the VHPs, perceptions of the utility of the men-only and couple sessions, and recommendations for the program. This was part of the process evaluation component to assess quality of delivery and response to program. A weakness of this assessment was lack of measures focused on GE elements of the intervention. For the participant satisfaction surveys, most men assigned to receive CHARM also provided survey responses (84.9 %; n/n = 398/469). Most responders (87.2 %; n/n = 347/398) had participated in CHARM and were able to provide feedback on their experiences of intervention delivery

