The three VHP-based CHARM intervention sessions were to be completed within a three month timeframe for all intervention arm participants. Most men recruited from CHARM communities (91.3 %) received Session 1 of CHARM; 77.2 % received Session 2, and 52.5 % received the couple’s session with their wife. Follow-up survey assessments were conducted at 9&18 months post-baseline with couples from both comparison and treatment clusters using the same procedures described above for baseline data collection; no additional referrals were provided at these time points unless requested. Additionally, at 18 month follow-up, wives were tested for pregnancy; pregnancy tests were obtained at only two time points to reduce costs and burden for interviewers. Also at 18 month follow-up, a subsample of couples (two couples per intervention village) were randomly selected to participate in in-depth interviews subsequent to their surveys; interviews assessed how the intervention affected the way the couple considers, discusses and uses family planning methods in their relationship. CHARM-trained VHPs (*n* = 16) participated in brief in-depth interviews subsequent to completion of the study to assess their perceptions of how the intervention affected family planning practices among rural young men and their wives. From March to December 2012, baseline data were collected. Subsequently, 9 month follow-up data collection was collected from November 2012 to September 2013, and 18 month follow-up surveys were collected 9 months after those dates. Of the 1081 couples participating in baseline assessment, 83.1 % (*n* = 898) and 82.4 % (891 couples) completed 9 and 18 month follow-ups, respectively [See Fig. 3. Consort Flowchart.].

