A data and safety monitoring plan was also in place and focused on two major safety aspects: 1) assurance that no harm came to participants as a result of survey or program participation and 2) assurance that all data collected from this project, including process and quality assurance data as well as outcome data, would maintain the privacy of research participants. To ensure no harm, and with recognition of high rates of domestic violence in India, at the time of each survey data collection, participants were assessed for immediate health and social service needs in the areas of FP, maternal or antenatal health, and violence, by research staff trained to provide referrals and links to health and social services, in accordance with the WHO guidelines for ethical research on domestic violence [37]. Participants were also notified via informed consent that their withdrawal from the program would not affect their participation in the survey participation and vice versa. Also, withdrawal from both the program and the survey participation would have no impact on the services they received at the local health clinic or within their work organization. Through informed consent, participants were additionally notified of research staff they could contact should any difficulties arise through their participation in this project. We did not anticipate that the surveys or medical record reviews would cause harm to enrollees, but the IRBs from all partnering institutions involved in this study (NIRRH, ICMR, Population Council and UCSD) had strict reporting requirements for adverse events and a yearly reporting process with which we complied with at all times. Multiple efforts were made across all study phases to reduce risks for adverse events. However, a data and safety monitoring plan was used to identify such events if they did occur. The plan was as follows: Should an adverse event be identified, the principal investigators from each site were to be notified within 48 h, and then there was to be a discussion that week whether the adverse event had anything to do with the research study (e.g., a death due to subject’s occupation), or whether it occurred as a consequence of an individual’s study participation (e.g., abuse of a participating wife subsequent to intervention involvement). IRBs and funders were to be notified immediately following the discussion. If it were the latter, considerations of how to reduce such risks in the future were to be determined and protocols were to be altered accordingly. No adverse events occurred, so the plan never required operationalizing.

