#### Analytic plan

Outcome analyses were designed to focus on the following outcomes of interest: spacing contraceptive use and communication, and included pregnancy, intimate partner violence and attitude outcomes based on women’s reports and pregnancy testing. The primary comparison of the outcomes by treatment group at 9 and 18 month follow-ups were done using mixed-effects regression models, with a nested random effects structure for the geographical clusters and for each couple within the cluster, over time. The treatment effect was evaluated via a time-by-treatment arm interaction. A categorical time effect was used (profile model). This treatment effect can be interpreted as the individual-level effect of the intervention. In addition, generalized estimating equations (GEE) logistic regression models with the same clustering and mean model structure and exchangeable working correlation matrix was used to express the intervention effect at the population level. Secondary analyses adjusted for relevant covariates to improve precision and possibly reduce bias. Demographic and fertility variables (e.g., age, current pregnancy, past year childbirth, etc.) were considered for inclusion in adjusted analyses, in addition to time and treatment arm, using backward model selection at the 0.15 threshold level. Bivariate analyses were conducted to assess differences in demographics, fertility history, and outcomes at baseline: 1) by treatment group, 2) for those lost to study follow-up, and 3) for CHARM participants lost to intervention. Any characteristics identified as significantly different between groups were considered as potential covariates in these adjusted models. Outcome analyses used an intent-to-treat approach and analyzed all subjects according to randomized group. Additional analyses were conducted based on receipt of intervention. All analyses used women’s data only, but men’s data will be used to validate findings on contraceptive behavior outcomes. All analyses were conducted using SAS (SAS Institute, Version 9.4, Cary, NC, USA).

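### The 12-month partner-violence recall reaches 3 months before baseline at the 9-month visit, pulling that contrast towards no difference; the 18-month window is clean

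*Protocol article*

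**What the plan says.** All the relevant text is in the protocol article.

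- **Measure.** Under Quantitative measures, the sentence introducing Table 2 covers every survey round: "Baseline and follow-up surveys were collected from couples using measures based on" national survey items or other validated tools. The partner-violence row, asked of women only, reads "11 items assessed physical and sexual marital violence, ever and in past 12 months". No shorter or since-baseline recall is given for follow-up. The contraception item in the same table uses a 3-month recall.
- **Timing.** Under Procedure: "Follow-up survey assessments were conducted at 9&18 months post-baseline with couples from both comparison and treatment clusters".
- **Outcome and comparison.** The Analytic plan says the outcomes of interest "included pregnancy, intimate partner violence and attitude outcomes", and then: "The primary comparison of the outcomes by treatment group at 9 and 18 month follow-ups were done using mixed-effects regression models". Time is categorical and the effect is a time-by-arm interaction, so the 9-month contrast is estimated in its own right. A logistic GEE model with the same mean structure is also specified.
- **Safety.** The section on IRB approval and ethical treatment gives abuse of a participating wife as an example of a study-related adverse event, and concludes: "No adverse events occurred, so the plan never required operationalizing".

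**The concern.** A 12-month look-back does not fit inside 9 months of follow-up. A wife whose only violence in the period came in the 3 months before enrolment still counts as positive at 9 months, whatever happened afterwards. Those same 3 months lie inside the baseline survey's own recall, so one event can count at both visits. Adjusting for baseline violence does not remove it from the 9-month outcome.

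In a randomised comparison the expected result is dilution, whether the true effect is a benefit or a harm. A chance baseline imbalance would also carry forward into the 9-month result. The programme counsels men on gender equity, and the Background section treats partner violence as a key target of such work. A flat 9-month result could therefore be read as no effect, or as reassurance on harm, when part of the flatness comes from the recall window.

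**Working it through.** **Inputs from the article:** recall 12 months; visits at 9 and 18 months. **Assumed, because the article gives no violence rate:** 12-month prevalence of 20% in controls, constant event rate, rate ratio 0.5 once the effect begins. The article states no figure for violence that could be reproduced first.

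**Step 1: window.** Pre-baseline share = max(0, 12 − visit month)/12.
- 9 months: 3/12 = 25% (window from month −3 to month 9). A visit at 8 or 10 months would give 33% or 17%.
- 18 months: 0% (window from month 6 to month 18).

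**Step 2: comparator.** The fair comparator for the 12-month item at 9 months is an item asking only about the 9 months since baseline. A 12-month period spent wholly under the effect is not a fair comparator, because no 9-month visit can contain one.

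**Step 3: formulas.** λ = −ln(0.8) = 0.2231 per 12 months. Let d be the months from baseline until the effect starts.
- Since-baseline item: control 1 − exp(−λ·9/12); intervention 1 − exp(−λ·[d + 0.5(9 − d)]/12).
- 12-month item: control 20%; intervention 1 − exp(−λ·[3 + d + 0.5(9 − d)]/12).

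| Effect starts | Item | Control | Intervention | Risk difference (points) | Risk ratio |
|---|---|---|---|---|---|
| Baseline (d = 0) | since baseline | 15.4% | 8.0% | −7.4 | 0.52 |
| Baseline (d = 0) | past 12 months | 20.0% | 13.0% | −7.0 | 0.65 |
| After month 3 (d = 3) | since baseline | 15.4% | 10.6% | −4.9 | 0.69 |
| After month 3 (d = 3) | past 12 months | 20.0% | 15.4% | −4.6 | 0.77 |

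The difference loses 0.4 points (7.38 to 6.98) or 0.3 points (4.85 to 4.59). The relative effect loses more because the pre-baseline months add about the same number of positive wives to both arms. The GEE model reports odds ratios, so the relative scale matters: with d = 0, (8.03/91.97)/(15.41/84.59) = 0.48 becomes (13.02/86.98)/(20/80) = 0.60.

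**Step 4: range.** For a halved rate at 10% to 30% prevalence, the risk ratio moves from 0.51–0.53 to 0.64–0.67 (d = 0), or from 0.68–0.70 to 0.76–0.78 (d = 3). The difference loses between 0.1 and 0.9 points. A rise in violence is diluted in the same way: at 20% prevalence, rate ratio 1.5 and d = 0, the risk ratio goes from 1.44 to 1.32 and the difference from 6.8 to 6.4 points.

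**Step 5: persistent violence.** Step 3 treats events as independent over time. If instead violence recurs in the same marriages and the effect is to stop it, a wife with any event in the 3 pre-baseline months stays positive. If a share q of positive wives had such an event, only 1 − q of the effect can show: 75%, 50% or 25% for q = 25%, 50% or 75%. The article gives no information on q.

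**The case against.** **The 9-month violence contrast is partly inferred.** The sentence naming 9 and 18 months covers all outcomes, and it cannot bind each one to both visits, since pregnancy tests were done only at baseline and 18 months. The questionnaire and full analysis plan are not shown. This has some force. However, Table 2 gives visit times for the pregnancy test and no restriction for violence, and the article prints both the recall and the comparison times. The mismatch is in the text and is not a detail left to another document.

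**The damage is limited.** Violence is not a sample-size outcome, and the 18-month contrast is planned and clean. Both points stand.

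Four stronger readings are tempting, and the article does not support them.

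- *Half of the 9-month window is unexposed*, because "sessions were to be completed within a three month timeframe for all intervention arm participants". The article places all core information in Session 1, makes Sessions 2 and 3 optional, and refers men to the provider directly after the baseline survey. Months 0 to 3 are exposed time and belong in an intent-to-treat comparison. Only the 25% is defensible.
- *The recall window halves the effect.* Under the assumptions above, 12 full months at half rate would give 10.6% against 20%, or 9.4 points, against 4.6 observed at 9 months with a delayed effect. Most of that gap comes from shorter follow-up and the assumed delay. Perfect since-baseline recall would itself give only 4.9.
- *The lifetime item is misused as an effect outcome.* Table 2 lists it as collected; the Analytic plan does not name it as an outcome.
- *Survey reports of violence were left out of the adverse-event statement.* The article does not say so. It describes a needs assessment covering violence at each survey, and a reporting pathway. It does not describe how survey answers fed that pathway, but silence does not show that they were excluded.

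**Conclusion.** The concern holds for one of the two follow-up contrasts. At 9 months a quarter of the recall window precedes baseline and overlaps the baseline survey's window, so the contrast is biased towards no difference. At 20% prevalence and a halved rate, the risk ratio moves from 0.52 to 0.65, or from 0.69 to 0.77 with a delayed effect, and the risk difference falls by 0.3 to 0.4 points. These sizes rest on assumed prevalence, rate ratio and constant rate; persistent violence would make the loss larger. The direction does not depend on the exact values. The 18-month contrast and the sample-size calculation are unaffected. It is worth correcting because the change is cheap and the outcome bears on both benefit and harm.

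**What to change.** 1. Make the 18-month past-12-month item, adjusted for baseline past-12-month violence, the basis for inference on partner violence.
2. Keep the 9-month result, but label it wherever it appears as covering 3 months before baseline. It should not be dropped: the 18-month item misses months 0 to 6, which include the delivery period.
3. For safety, report by arm new past-12-month violence at both 9 and 18 months among wives who reported none in the past 12 months at baseline. Apart from recall error, a new report at 9 months in this group should be post-baseline, and so it covers the months that the 18-month item misses.
4. Refer to that table beside the statement that no adverse events occurred.

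Study procedures are complete, so no new data are needed. The cost is some analysis wording, one table, and less weight on the 9-month violence contrast.

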#### Quantitative data collection, management and analysis

Baseline survey data were collected on paper. Paper surveys were reviewed by research staff immediately subsequent to data collection to ensure completeness. Paper surveys were transported nightly to the local office in rural Vasai, and transported weekly to the data management office in Mumbai, for data entry. For every survey collected, research staff noted date of collection, assigned participant identification number, interviewer initials, and location of data entry, into the survey (Vasai office or transported to Mumbai for data entry). All hard copy surveys were maintained in a locked file in the research offices. Masters-level staff conducted double data entry, with consistency checks and verifications performed on an ongoing basis, to ensure high quality data. Although the plan was for collected data to be entered within a month of collection, in practice, data entry staff were responsible for other project tasks and unable to maintain consistent data entry during baseline data collection. Much of the baseline data were entered over the course of the eight months following completion of baseline data collection. Periodic (bimonthly) reviews of entered data in descriptive format were shared with the study team for quality assurance. The plan was to use Perseus for mobile data collection, but lack of Marathi font impeded our ability to use this software.

For 9&18 month follow-up survey data collection, our study team worked with software engineers at Qualcomm Institute, University of California—San Diego, to create the MSHARE (Mobile Survey for Health Assessment, Research and Evaluation) System, for electronic data collection and web-based data management. This system was designed to display any font in any language. The CHARM surveys were coded using XML into the android operating system-based MSHARE System. The MSHARE application with the CHARM survey questionnaire was then loaded onto the tablets, displaying questions simultaneously in English and Marathi, to help ensure clarity of the questions for our bilingual research staff. MSHARE captured data more accurately than paper surveys, and allowed for uploading of data to a web-based data management system for real time data sharing, such that the US and Indian investigator teams had access to data simultaneously from any location with internet access. Each field researcher maintained their own android tablet to collect and store data, short-term. The memory available in tablets allowed the field researcher to save hundreds of completed surveys for a 25–30 page survey. At the end of each day of data collection, the field researcher brought their tablets to a field research site to upload the data via internet. Lack of Wi-Fi availability in rural Vasai impeded immediate upload in the field, though MSHARE allowed for this capacity had Wi-Fi been available. Conversion to MSHARE allowed 9 month-follow-up data collection completed in October to be presented at a conference in November. Uploaded data were monitored weekly for assurance of transfer into the MSHARE database, and data were analyzed monthly and presented to the research team for quality review and discussion.

#### Labeling and tracking data

All data collected in the study, whether on paper or tablet, were labeled with a unique identifier to de-identify the data but allow linkage of longitudinal data from the same subject and data from husbands and wives. Identifiers were linked with participant contact information to support tracking and linkage, but kept in a locked file at the local research office in India, to facilitate follow-up by the field team, as needed. All labeling and tracking information, minus identifiers, were kept in a log with a schedule of study assessments populated, and notification of date of data collection at each time point. This was monitored and tracked daily by the field site supervisor to monitor recruitment and follow-up rates throughout the study. Monthly meetings with VHPs included collection of participant session participation, which was then linked to this monitoring sheet to observe study participation. These data were used for dose analyses in the evaluation. The full monitoring sheet was reviewed on weekly calls between the US and Indian investigator teams throughout the course of data collection for this study.

